### Ethical issues

The Ethics Committee of the FJTCM approved this protocol (Approval No. 2012–031). Each participating center will obtain local institutional review board approval. All study participants will sign an informed consent sheet prior to participation.

### Baseline measurements

Baseline descriptive data will be obtained via a questionnaire (Table 1).

**Table 1 T1:** Baseline descriptive data

**Data**	**Content**
General data	Agent of the person who conducted test, test start date, the patient’s address, name of accompanying family members and the patient’s telephone number
Demographic data of subject	Gender, age, nationality, level of education, profession, height and weight
Assessment of knee before test	Visual analogue scale (VAS), knee girth, knee’s range of motion (ROM), manual muscle test (MMT), stair-climbing ability, walking distance, comprehensive effect, average daily amount of non-steroidal anti-inflammatory drugs taken, activities of daily living (ADL), quality of life (QOL), safety assessments and economic evaluation
Other	Complications, medication use, previous treatment and duration of KOA symptoms

### Interventions

The participants in the experimental group will undergo CTCMRP rehabilitation treatment. This consists of Chinese medical herb fumigation-washing, traditional exercises (developed from simplified t’ai chi and *yi jinjing*), acupuncture and *tuina*. Patients in the control group will undergo CT rehabilitation including physical factor therapy and kinesitherapy. The duration of rehabilitation will be 4 weeks, which is a common duration in clinical practice. During the rehabilitation period the therapist will monitor proper performance, exercise intensity and will progress the exercises, if necessary.

### Health education

Two strategies will be used for health education: (1) Educational brochures on KOA, published by FJTCM, will be sent to participants. Information in these brochures will include the concept, epidemiology, etiology, common symptoms, diagnosis, treatments and precautions that should be taken. (2) The rehabilitation therapist will introduce and explain the contents of the educational brochures to all participants in person.

The aim is to help participants learn about and understand KOA and to implement strategies to help alleviate the disease. Moderate activity, aerobic training (swimming), avoidance of long periods of running or jumping, decreasing or avoiding climbing stairs, and reducing weight if necessary, can all help to improve KOA.

### Experimental group

The experimental group will be treated according to the CTCMRP (Table 2).

**Table 2 T2:** TCM rehabilitation based on syndrome using appropriate technology

**Symptom**	**TCM rehabilitation treatment**
Diagnosis of KOA and inclusion and exclusion criteria	Basic rehabilitation: Chinese medical herb fumigation-washing + traditional exercises (developed from simplified t’ai chi and *yi jinjing*)
Swelling (mild to moderate by knee girth)	Basic rehabilitation + bloodletting by puncturing and cupping
Weak muscle strength (over 3 degrees by MMT)	Basic rehabilitation + *tuina*
Pain (over 5 by VAS)	Basic rehabilitation + acupuncture

In all cases, Chinese medical herb fumigation-washing with traditional exercises (to a basic prescription) will be used. If there is significant swelling in the joint, basic rehabilitation plus cupping and bloodletting will be used. When there is a significant decrease in joint strength, basic rehabilitation plus *tuina* will be used. When there is significant joint pain, basic rehabilitation plus acupuncture will be used.

#### Chinese medical herb fumigation-washing

The right or left knee joint will be washed twice daily, for 6 days, with a decoction of *hai tong pi*[24]. The recipe for this is: *Erythrina indica* Lam (15 g), moxa (15 g), *Phryma leptostachya* (15 g), *Lycopodium clavatum* (15 g), radix aconiti (10 g), radix aconiti agrestis (10 g), *Pericarpium zanthoxyli* (10 g), radix angelicae (10 g), radix clematidis (10 g), cassia twig (10 g), safflower carthamus (5 g) and *Ligusticum wallichii* (5 g). Patients will undergo a 6-day course of treatment on four separate occasions (Table 3).

**Table 3 T3:** **Traditional exercise intervention** (**developed from simplified t**’**ai chi and *****yi jinjing***)

**Phase**	**Description and progression**
Phase 1: foot and heel jolt	(i) Stand at attention, heel lift up and look forward for 10 seconds
	(ii) Move the heel back down, tap the ground slightly and keep looking forward
Phase 2: rotate knee	(i) Stand at attention, slightly bend knees, put hands on the ipsilateral knees and look forward
	(ii) Circular movement of knee
Phase 3: heel kick	(i) Lie down with leg bent and hands lying naturally at the side of the body
	(ii) Bend at the hip joint and at the knees, extend the back of the ankle for 15 seconds, kick up the heel while moving the toes toward the shin (plantar flexion) and straighten the knee as far as possible. Do this one leg at a time

#### Traditional exercises

Simplified t*’*ai chi and yi jinjing exercises will be performed twice daily with each patient completing one set of 15 repetitions for both knees (Table 3).

#### Cupping and bloodletting intervention

Patients will undergo cupping as well as being punctured for bloodletting. This will be done twice weekly, at points ST 34 and SP 10, using a percusso-punctator. This will not be done in patients with skin ulcers, dermatitis or hemophilia.

#### Tuina

This treatment is based on the theory of meridians and will be done once a day (15 repetitions of 3 to 5 minutes each) as in clinical practice (Table 4).

**Table 4 T4:** **
*Tuina *
****intervention**

**Location**	**Description and progression**
Bladder meridians	Thumb and fingers rub the points from BL 37 to BL 56
Stomach meridians	Thumb and fingers rub the points from ST 34 to ST 36
Spleen meridians	Thumb and fingers rub the point from SP 9 to SP 10
Around the knee	Push the muscle and warm using the palm of the hand and the base of the thumb (the thenar eminence) repeatedly

#### Acupuncture

Patients with a pain score over 3, according to the VAS scale, will undergo acupuncture. While the patient is lying down, needles will be inserted into the following acupuncture points: Ex-LE 5, Ex-LE05, Ex-LE 2 and Ashi. The treatment will last 30 minutes and will be carried once per day. Single-use Huatuo needles (0.35 × 40 mm) will be used and will be disposed of into a bedside sharps container upon completion of treatment.

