### Exclusion criteria

Patients are excluded if they have:

•severe knee swelling

•a muscle strength of grade 2 or below according to a manual muscle test

•a history of trauma to the knees

•serious heart, kidney, liver or nervous system disease, or lower limb gangrene due to diabetes.

•lower limb dysfunction caused by spinal, hip or ankle joint disease, or prior knee joint surgery

•a tumor of the knee joint

•a cognitive or psychological disorder

•received traditional exercise training and/or *tuina* for the knee within the last 4 weeks

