### Recruitment

Outpatients with KOA will be recruited from participating CHCs in China. All participants will be selected according to the above inclusion and exclusion criteria. Baseline measurements will include the general and demographic data for the subjects, assessment of the knee prior to testing, medication use, previous treatments, KOA complications and duration of KOA symptoms. Due to ethical considerations, non-steroidal, anti-inflammatory drugs will be permitted (and registered) as required for patients with visual analogue scale (VAS) scores over 5. All patients will be asked to refrain from seeking other forms of treatment during the trial. During the follow-up period, patients will be asked to report whether they have received other forms of treatment.

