### Primary outcomes

Average knee pain will be self-assessed using a 100 mm visual analogue scale (VAS) with terminal descriptors of ‘no pain’ and ‘worst pain possible’. The VAS pain measurement has demonstrated reliability in KOA [27].

Knee girth will be determined using a flexible plastic measuring tape to measure the transverse plane circumference of the knee at the mid-patellar height, with the patient in a supine position. Girth measurement has shown acceptable reliability for determination of gross changes in knee swelling after knee surgery [28].

The knee’s range of motion (ROM) will be measured using a standard long-arm goniometer. To determine knee flexion ROM, patients will be asked to slide the heel actively towards the buttocks and maximal active knee flexion will be measured. Knee ROM in patients with KOA has been shown to be adequately reliable with a coefficient of 0.96 for flexion and 0.81 for extension [29].

The manual muscle test (MMT) will be performed according to Medical Research Council (MRC) guidelines [30]. The British MRC has developed a muscle scale that grades muscle strength between 0 and 5 [31]. According to the muscle scale, 0 = no palpable contraction, total paralysis; 1 = flicker or trace of muscle contractions; 2 = active movement with gravity eliminated; 3 = full range with gravity eliminated; 3– = partial range against gravity; 3+ = full range against gravity with no resistance possible; 4 = slight resistance; 4– = mild resistance; 4+ = moderate resistance; 5– = barely detectable weakness and 5+ = normal motor power.

Walking performance will be assessed using the six-minute walking test (6 MW). This measures the distance that participants are able to walk in 6 minutes while wearing their usual footwear. Patients will be allowed to use a cane, if necessary. Standardized feedback will be provided to patients during each test as described previously [32]. The 6 MW test will be done twice and the test results averaged. A longer walking distance than baseline will indicate better walking performance. The 6 MW test has excellent test-retest reliability from 0.95 to 0.97 and a low coefficient of variation (10.4%) [33].

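### Acupuncture is triggered at VAS over 5 in Table 2 but over 3 in the Acupuncture section, and neither cut-off has a unit on the 100 mm scale

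*Protocol article*

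**What the plan says.** Table 2 (section Experimental group) gives every experimental participant a base treatment and adds components by symptom.

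- **Acupuncture, Table 2:** the row is headed "Pain (over 5 by VAS".
- **Acupuncture, text under Table 2:** "When there is significant joint pain, basic rehabilitation plus acupuncture will be used". No number is given.
- **Acupuncture, section of that name:** "Patients with a pain score over 3, according to the VAS scale, will undergo acupuncture". The session lasts 30 minutes and is given once a day.
- **The scale (Primary outcomes):** "Average knee pain will be self-assessed using a 100 mm visual analogue scale (VAS". No other VAS is described.
- **Anti-inflammatory drugs (Recruitment):** permitted "as required for patients with visual analogue scale (VAS) scores over 5".
- ***Tuina*, Table 2:** "Weak muscle strength (over 3 degrees by MMT". The text below the table says "When there is a significant decrease in joint strength, basic rehabilitation plus *tuina* will be used".
- **Muscle strength at entry (Exclusion criteria):** patients are excluded for "a muscle strength of grade 2 or below according to a manual muscle test". The grading under Primary outcomes rises from 0 to 5+, which is normal power.

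**The concern.** Two current rules for the same arm give different answers for the same participant. The component at issue is a daily treatment that could plausibly affect pain, one of the listed primary outcomes.

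The trial is described under Study design as cluster randomized, with treatment delivered in CHCs, and Sample size gives 38 of them. If centers follow different rules, the content of the experimental package varies between clusters. The final report then could not say which trigger was tested. This matters more than usual here, because the stated aim is a standard protocol that other centers can adopt.

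The missing unit adds to the problem. The same bare number also governs drug use, and average daily drug consumption is a secondary outcome.

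**Working it through.** The plan calculates no figure on this point, so there is none to reproduce. The check compares the passages and then sizes the disputed group under stated assumptions.

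**1. The acupuncture rules side by side (0–10 reading)**

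| Participant's VAS | Table 2 (over 5) | Acupuncture section (over 3) |
|---|---|---|
| 3 or below | no | no |
| above 3, up to 5 | **no** | **yes** |
| above 5 | yes | yes |

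The text under the table has no number, so it cannot decide the middle row.

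**2. Size of the middle row**

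The article gives no baseline VAS distribution. Assume a normal distribution with mean μ and SD σ, truncated to 0–10:

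share = [Φ((5−μ)/σ) − Φ((3−μ)/σ)] / [Φ((10−μ)/σ) − Φ((0−μ)/σ)]

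The experimental arm is 722/2 = 361, since Sample size plans equal groups.

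| μ | σ = 1.5 | σ = 2 | σ = 2.5 |
|---|---|---|---|
| 4 | 49.7% (179) | 39.2% (142) | 33.2% (120) |
| 5 | 40.9% (148) | 34.6% (125) | 30.2% (109) |
| 6 | 23.1% (83) | 24.8% (89) | 24.5% (88) |
| 7 | 8.9% (32) | 14.6% (53) | 17.8% (64) |

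Worked example for μ = 4, σ = 1.5: the numerator is Φ(0.667) − Φ(−0.667) = 0.495 and the denominator is Φ(4) − Φ(−2.667) = 0.996. The ratio is 0.497, and 0.497 × 361 ≈ 179.

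**3. Literal reading in millimeters**

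Use P(VAS > c) = 1 − Φ((c − μ)/σ), with an assumed mean of 50 or 60 mm and SD 20 mm.

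- Mean 50: P(>5 mm) = 1 − Φ(−2.25) = 0.988 and P(>3 mm) = 1 − Φ(−2.35) = 0.991.
- Mean 60: P(>5 mm) = 1 − Φ(−2.75) = 0.997 and P(>3 mm) = 1 − Φ(−2.85) = 0.998.

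In millimeters the two cut-offs differ by 0.3 percentage points or less, but almost everyone would receive acupuncture and almost everyone would qualify for the drugs. So the unit also decides who is treated.

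**4. The *tuina* row**

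Higher grades mean greater strength. With grade 2 or below excluded, eligible participants run from about grade 3 up to 5+. The bracketed criterion, taken alone, covers everything above 3, including normal power, and does not cover grade 3 itself. The row label and the text below the table both speak of reduced strength, but neither gives an upper limit or says how grade 3 is handled.

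**The case against.** **The scale.** A 100 mm line is 10 cm, and cut-offs of 3 and 5 sit naturally on a 0–10 reading. A therapist is unlikely to treat 5 mm as significant pain. This stands: the missing unit is mainly a matter of clarity, and the literal millimeter reading is improbable. It does not remove the conflict, because the 0–10 reading is the one on which 3 and 5 differ most.

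**Tailoring and central training.** Components differ between participants by design, and the randomized contrast is a tailored package against conventional therapy. One university trains and supervises therapists at all sites, and the Discussion describes accreditation and regular meetings. This also stands in part. A reader might infer that CHCs do in fact diverge, that the experimental arm is not one intervention, or that no standard could follow from the result. The article supports none of these. It shows only that the text permits divergence. Training may have settled on one rule, but the article does not say which.

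***Tuina*.** A reader might infer a flat contradiction in which the rule picks the strongest participants and leaves out the weakest. That requires ignoring the word that labels the row. The bracket can be read as the eligible range, as in the swelling row, where mild to moderate mirrors the exclusion of severe swelling. What remains is an unclear criterion.

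**Magnitude.** Any single percentage depends on a VAS distribution that the article does not give. This is correct, and only the range should be quoted.

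**Conclusion.** The conflict between Table 2 and the Acupuncture section is established from the text alone and needs no assumption. As written, the acupuncture rule is not uniquely defined for participants above 3 and up to 5 on a 0–10 reading.

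Its size is illustrative: about 9% to 50% of the experimental arm (32 to 179 of 361), for assumed means of 4 to 7 and SDs of 1.5 to 2.5. Any resulting increase in between-center variation cannot be calculated from the article, and no input to the sample size formula is changed.

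The missing VAS unit, including in the drug rule, is confirmed and needs correcting. The *tuina* wording is a lesser point of clarity. No view is taken here on which cut-off is right.

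**What to change.** The sponsor must:

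1. Reconcile Table 2 (and the text under it) with the Acupuncture section, so that one pain trigger applies.
2. Express every VAS cut-off in Recruitment, Table 2 and Acupuncture in the units of the 100 mm scale.
3. Reconcile the muscle-strength wording in Table 2 with the text below it and with the exclusion criterion, so that the handling of grade 3 and of normal strength is clear.
4. Notify all CHCs of the clarified text, with its date.

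The clinical team chooses the values.

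**Cost.** This is a protocol clarification and a notice to therapists. Recruitment is ongoing, so the clarification may change who receives daily acupuncture at some centers. Participants treated before it may have been handled under a different reading. The dated notice lets the report separate the two periods and describe this openly.

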### Control group

The control group will be treated with physical factor rehabilitation and kinesitherapy [22,25].

#### Thermal design power

Participants will be asked to undergo *Te Ding Dian Ci Pu* (TDP, a machine that can release specific frequency of electromagnetic wave to treat disease) for at least 30 minutes per day. The distance between the TDP and the knee must be from 30 cm to 50 cm.

#### Kinesitherapy

Kinesitherapy is designed to strengthen lower limb muscles and incorporates exercises commonly used in clinical practice. It is based on clinical trials showing that such exercise programs can reduce pain and improve function [26]. The aim of kinesitherapy is to strengthen the quadriceps, hamstrings and other muscles around the knee. Participants will do this twice daily under the direction of the therapist (Table 5).

**Table 5 T5:** Kinesitherapy

**Intervention**	**Description**
Passive movement	(i) The patient sits on a bed with the limb hanging over the edge of a bed. A rolled towel or pad is placed under the shallow depression at the back of the knee joint (popliteal fossa).
	(ii) The therapist holds the bottom (distal) of the lower leg and pulls toward the foot for 10 seconds. This is repeated five times consecutively.
	(iii) The therapist uses his or her hands to flex and extend the knee. Patients will be informed that this will be a passive motion and may uncomfortable but should not be painful.
Active movement	(i) The participant lies on his or her back, lifts and straightens one leg with a weight attached to the ankle. The heel is lifted so that it is approximately 18 cm above the bed and held in that position for 30 seconds. This is repeated three times consecutively.
	(ii) The participant lies on his or her back, stretches out the knee and performs a set of 15 quadriceps contractions keeping the leg in the same position. This is repeat twice a day for 4 weeks.

### Timelines

Project funding was approved in July 2012 and commenced in October 2012. Ethics approval was obtained from the Medical Ethics Committee of FJTCM in September 2012. Recruitment commenced in October 2012 and will be completed in October 2013. The trial is due for completion in October 2015 at which time all participants will have completed the 3-month follow-up. Outcomes will be assessed at baseline, and at 4-, 10- and 12-weeks post-baseline. Telephone contact and follow-up clinic visits will be used to assess participant adherence to the study protocol.

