**Method/design:**

This will be a randomized controlled clinical trial with blinded assessment. There will be a 4-week intervention utilizing rehabilitation protocols from traditional Chinese medicine and conventional therapy. Follow-up will be conducted for a period of 12 weeks. A total of 722 participants with knee osteoarthritis will be recruited. Participants will be randomly divided into two groups: experimental and control. Primary outcomes will include range of motion, girth measurement, the visual analogue scale, and results from the manual muscle, six-minute walking and stair-climbing tests. Secondary outcomes will include average daily consumption of pain medication, ability to perform daily tasks and health-related quality-of-life assessments. Other outcomes will include rate of adverse events and economic effects. Relative cost-effectiveness will be determined from health service usage and outcome data.

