## Methods/design

### Study design

This will be a cluster randomized controlled trial with blinded assessment (Figure 1). The trial will comprise a 4-week intervention, using the CTCMRP and conventional therapy (CT), and a 12-week follow-up period. The protocol will be conducted at CHCs run by the Affiliated People’s Hospital of Fujian University of Traditional Chinese Medicine (Fujian province, China), the Comprehensive Traditional and Western Medicine Hospital of Guangdong province (Guangdong province, China), the Chengdu Military Region General Hospital of the Chinese People’s Liberation Army (Sichuan province, China) and the First Affiliated Hospital of Guangzhou University of Traditional Chinese Medicine (Guangdong province, China). To include a broad range of patients, this protocol includes CHCs in different areas. Fujian University of Traditional Chinese Medicine (FJTCM) is responsible for training and supervising rehabilitation therapists at all clinical sites. The evidence-based medicine center, which will be used for documentation and data analysis, is an independent site that performs data monitoring, randomization and statistical evaluation and will be blind to the intervention. Patients will be recruited through CHC outpatient clinics. The Human Research Ethics Committee at Fujian University of Traditional Chinese Medicine (Fujian province, China) approved the study.

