### Follow-up

During the 12-week follow-up period, trained personnel will contact the participants each week via telephone. Participants will be asked about the KOA and whether they have received other treatments. Participants will be asked to attend a follow-up clinic at 6 and 12 weeks to assess pain, swelling, range of motion, muscle strength, average walking distance, stair climbing ability, activities of daily living (ADL), quality of life (QOL) and medication usage.

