### Statistical analysis

Statistical analysis will be conducted using SAS software (version 8.2, SAS Institute, Cary, NC, USA). All tests will be two-tailed with *P* values of less than 0.05 considered statistically significant.

Descriptive statistics will be presented for each group as the mean ± standard deviation and all enumeration data will be presented as constituent ratio and rate in the outcomes from baseline to each time point. Changes in differences between groups in the primary and secondary outcomes, before and after treatment and during the follow-up period (at 4 weeks and 12 weeks), will be analyzed using repeated measures ANOVA or a rank-sum test.

Changes in effect sizes between pre- and post-intervention will be performed using the Wilcoxon test and chi square test. The effect size will be evaluated with safety set (SS), full analysis set (FAS), per-protocol set (PPS) and cost-effectiveness analysis. Demographic and CHC characteristics, as well as baseline data, will be analyzed using the FAS to assess the baseline and CHC comparability between groups. The primary analysis of the data will be undertaken using FAS with the principle of intention-to-treat and the PPS. The secondary analysis of the data will be undertaken using PPS. To account for missing data, multiple imputation of missing follow-up measures will be performed per the methods used for missing data [41]. The PPS will be used to assess adherence, the SS to assess adverse events and the cost-effectiveness analysis to assess health economics.

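### Timelines and Follow-up give visit schedules that no single clock can reconcile, so the last assessment falls at week 12 or week 16 after baseline

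*Protocol article*

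**What the plan says.** Five places in the Protocol article bear on when outcomes are measured.

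- Study design: "The trial will comprise a 4-week intervention, using the CTCMRP and conventional therapy (CT), and a 12-week follow-up period". The abstract gives the same follow-up length: "Follow-up will be conducted for a period of 12 weeks".
- Timelines: "Outcomes will be assessed at baseline, and at 4-, 10- and 12-weeks post-baseline". The same section ties the end of the trial to a point "at which time all participants will have completed the 3-month follow-up".
- Follow-up: "Participants will be asked to attend a follow-up clinic at 6 and 12 weeks to assess pain, swelling, range of motion, muscle strength", together with walking distance, stair climbing, daily activities, quality of life and medication use. The section opens by describing what happens in the 12-week follow-up period, so the clinics belong to that period.
- Statistical analysis: between-group differences in primary and secondary outcomes are examined before and after treatment and "during the follow-up period (at 4 weeks and 12 weeks"), by repeated measures ANOVA or a rank-sum test.
- Discussion: one purpose of the follow-up is to learn whether benefit lasts beyond the treatment period.

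**The concern.** Timelines is explicit about its origin: weeks are counted from baseline. The Follow-up section counts within a follow-up period that appears to start when the 4 weeks of treatment end. Once both are put on one scale, the visits do not coincide. The last two visits are 2 weeks apart in Timelines and 6 weeks apart in Follow-up.

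At stake is the meaning of the final time point. A result labeled as 12 weeks could describe patients 8 weeks or 12 weeks after treatment stopped, and the answer on durability depends on which it is. Sites that read different sections could also schedule the final visit differently, and the label would then cover two times.

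**Working it through.** **Inputs.** Intervention 4 weeks and follow-up 12 weeks (Study design, abstract). Assessments at weeks 4, 10 and 12 from baseline (Timelines). Clinics at 6 and 12 weeks (Follow-up). Analysis times 4 and 12 weeks (Statistical analysis).

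**Formula.** Week from baseline = stated week + origin, where the origin is 0 if counting starts at baseline and 4 if it starts at the end of treatment.

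| Origin | Follow-up clinics (6, 12) | Match with Timelines (4, 10, 12) | Analysis times (4, 12) | Match with Timelines |
|---|---|---|---|---|
| Baseline (0) | 6, 12 | 12 matches, 6 does not | 4, 12 | both match; 10 not named |
| End of treatment (4) | 10, 16 | 10 matches, 16 does not | 8, 16 | neither matches |

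**Is there another origin?** The two clinics are 12 − 6 = 6 weeks apart. Among the Timelines visits the gaps are 10 − 4 = 6, 12 − 10 = 2 and 12 − 4 = 8. Only the pair (4, 10) has the right gap, and it needs an origin of 4 − 6 = −2, that is, a follow-up starting two weeks before baseline, which makes no sense. No origin at or after baseline fits.

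**Likely source.** 10 = 4 + 6 is the first clinic counted from the end of treatment. 12 is the second clinic without the 4 weeks added. Timelines therefore appears to mix two clocks; on one clock the second clinic would be at 4 + 12 = 16.

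**Size.** Final visit at week 12: 12 − 4 = 8 weeks after treatment. Final visit at week 16: 16 − 4 = 12 weeks after treatment. The difference is 4 weeks, or 4/12 = one third of the stated follow-up.

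**Do the calendar dates settle it?** No. Recruitment is to end in October 2013 and the trial in October 2015. Two years remain after the last enrollment, which accommodates either reading.

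**Analysis times.** Counted from baseline, they agree with Timelines but do not name the intermediate visit. Counted from the end of treatment, they give weeks 8 and 16, and no clinic is scheduled at week 8. Either way the intermediate visit (week 6 or 10), at which the Follow-up section collects the outcomes, is not named.

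**The case against.** The strongest reply is that an article condenses a fuller protocol, that the flow chart (not available in the text) may show the schedule, and that visit lists for a model commonly sit in an analysis plan. This does not remove the contradiction: the schedule is stated here, in numbers, and two sections disagree. It does limit what else can be claimed. A reader might infer any of the following, and the documents do not support them:

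- *That there are three mutually incompatible schedules.* The analysis times fit Timelines if both count from baseline, with week 4 as the after-treatment value and week 12 as follow-up. The firm contradiction is between Timelines on one side and Follow-up with Study design on the other.
- *That one visit is excluded from the analysis.* Statistical analysis does not name it, but nothing rules it out; the section also speaks of outcomes at each time point and of repeated measures.
- *That week 16 is certainly intended.* The abstract and Study design list treatment and follow-up separately, and week 10 fits only a clock starting at the end of treatment. No section, however, says when the 12 weeks begin.
- *That timing differs between arms.* Randomization by health center makes this possible in principle, but no section suggests that centers use different schedules. One university trains and supervises the therapists at all sites, and regular meetings are planned.
- *That the main comparison is compromised.* The sample size rests on the curative effect rate after rehabilitation, defined from scores before and after treatment. Week 4 is in both Timelines and Statistical analysis, and Follow-up does not conflict with it.

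**Conclusion.** The schedule is wrong as written. Timelines cannot be reconciled with Follow-up and Study design, and the last assessment is at week 12 or week 16 from baseline, 8 or 12 weeks after a 4-week treatment. The contradiction itself needs no assumption beyond an origin at or after baseline. The two candidate final weeks assume that follow-up is counted either from baseline or from the end of the 4 weeks of treatment.

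The consequence is confined to the sustained-efficacy question and to any result labeled as 12 weeks; the week-4 comparison stands. The silence of Statistical analysis on the time origin and on the intermediate visit is a secondary point that calls for clarification. The point should be settled while recruitment is still ongoing, as Trial status reports.

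**What to change.** The sponsor should confirm the intended schedule. Weeks 4, 10 and 16 from baseline is best supported by the abstract, Study design and Follow-up taken together, but this needs confirmation rather than assumption. Then:

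1. State all visits in weeks from baseline in Timelines, Follow-up and Statistical analysis.
2. List the intermediate visit among the repeated-measures time points.
3. Notify the 38 community health centers of the confirmed schedule.
4. Record the actual date of every assessment and use it in the analysis.

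The cost is mainly wording and a notice to sites, and the number of visits does not change. There is one downside. If sites have been working to week 12 and week 16 is confirmed, some participants may already have had their final visit at week 12, and the remaining final visits would move by 4 weeks. Step 4 allows the analysis to handle such a mixture openly.
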